### Health Economic Analysis

The economic analysis will be conducted from a health service perspective. Cost estimation will follow a categorize:quantify:value approach. In the absence of health service implications, the costs will reflect the resources required to generate, implement, and deliver the respective interventions. The valuation will be founded on the concept of opportunity cost, that is, the value of the benefit forgone in not employing labor, services, or materials in alternative uses. Market prices will be used as a proxy for this value. Labor costs will reflect relevant skills, such as dietician time and administration time, and will incorporate additional employee benefits such as superannuation. Services include expenditure such as Facebook advertising. Materials capture nonlabor cost items such as flyers. Costs will be reported separately and jointly.

If a statistically significant difference in AQoL-6D is found, a within-trial cost analysis will be conducted using quality-adjusted life years (QALYs) as the primary outcome. The incremental cost-effectiveness ratio (ICER) will report an incremental cost per QALY, reflecting the incremental outcome and cost differences between the comparator groups. The ICERs will be calculated as the arithmetic mean difference in cost between the intervention and control arm divided by the arithmetic mean difference in effect. Groups 2 and 3 will be compared individually with Group 1 and each other. If a significant change in AQoL-6D is not observed, the ARFS outcome measure will be used. If neither measure realizes a statistically significant change, the economic method will default to a cost-consequence analysis, with incremental costs reported against all primary and secondary outcomes. The economic analysis will be conducted, and the results will be reported in accordance with best practice guidelines [54,55].

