#### Economic Measures

There is no basis for anticipating that health service utilization will vary between trial arms as a result of the interventions. As a consequence, health service engagement is assumed to be randomized, and the requirement to collect health service engagement or medication use is excluded. The additional costs relating to the intervention and implementation of the intervention, including materials, labor, and other expenditures, will be collected through project management and project team records. The economic analysis will use either the change in ARFS or AQoL-6D as the outcome of interest. If the change in either is not statistically significant, all consequence measures, primary and secondary, will be reported alongside the cost estimates.

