### Sample Size

The sample size calculation was based on detecting changes in the primary outcome of diet quality score (AFRS), with adequate power to assess differences in daily servings of fruit and vegetables. The study aims for a between-group increase in ARFS of 2.2 (baseline SD 9.6) and fruit and vegetables serves per day of 0.56 (baseline SD 2.4) compared with no change in the control group [53]. To detect this between-group AFRS difference with an alpha of .05 and 80% power, 300 participants per arm across 3 arms are required, totaling 900 participants. Given that we also wish to examine this effect a priori in male and female subgroups separately, we will require 900 participants of each gender or 1800 in total. To allow for 10% loss to follow-up at 3 months, 20% at 6 months, and 30% at 12 months, the study requires a total sample of 2570 (1285 males and females each).

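### Whether a cost-per-QALY or cost-per-ARFS ratio is produced depends on statistical significance, which makes a reported ICER too favourable on average; the two economic sections also word the trigger differently

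*Protocol article*

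**What the plan says.** The rule appears in two places in the protocol article.

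**Health Economic Analysis** sets an ordered, three-step rule.
1. AQoL-6D comes first: "If a statistically significant difference in AQoL-6D is found, a within-trial cost analysis will be conducted", with QALYs as the outcome.
2. ARFS is the fallback: "If a significant change in AQoL-6D is not observed, the ARFS outcome measure will be used".
3. Last: "If neither measure realizes a statistically significant change, the economic method will default to a cost-consequence analysis", with incremental costs set against all primary and secondary outcomes.

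The ICER is the mean cost difference "divided by the arithmetic mean difference in effect", and "Groups 2 and 3 will be compared individually with Group 1 and each other", which makes three pairwise comparisons.

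**Economic Measures** gives no order: "The economic analysis will use either the change in ARFS or AQoL-6D as the outcome of interest". It then says: "If the change in either is not statistically significant, all consequence measures, primary and secondary, will be reported alongside the cost estimates".

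Neither section says which of the three comparisons, which time point or which alpha decides the switch. The Sample Size section is built on a "between-group increase in ARFS of 2.2 (baseline SD 9.6"), with fruit and vegetable serves also considered. It does not mention AQoL-6D. Cost-effectiveness is listed under the secondary aim.

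**The concern.** An ICER has the effect difference in its denominator. If the ratio is calculated only when that difference, or one closely related to it, is significant, the reported ratios come from the trials in which chance pushed the effect upwards. The denominator is then too large on average and cost per unit of effect too low. Writing the rule down in advance makes it transparent but does not remove the selection.

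The QALY ratio is the most exposed. The protocol ranks it first, yet the trial was sized for ARFS. A non-significant AQoL-6D difference would therefore be weak evidence of no QALY gain, but under this rule it removes the cost-per-QALY ratio altogether.

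The two sections also trigger the cost-consequence report differently: one when *either* measure is non-significant, the other when *neither* is significant. Read literally, they part company whenever exactly one measure is significant.

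**Working it through.** **1. The plan's own figure.** Inputs from Sample Size: difference 2.2, SD 9.6, alpha .05 (taken as two-sided), power 80%.

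n per arm = 2 × (1.960 + 0.842)² × 9.6² / 2.2² = 298.9, so 299, or 300 with the t distribution. The stated 300 reproduces. Allowing for 30% loss, 1800 / 0.70 = 2571.4, so 2572 against the stated 2570, which is a rounding difference. The sizing for ARFS is sound. There is no corresponding input for AQoL-6D.

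**2. Effect of the gate.** Let θ be the true effect divided by its standard error, and let the gate be |Z| > 1.96. With φ the standard normal density,

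mean reported effect / true effect = 1 + [φ(1.96 − θ) − φ(1.96 + θ)] / (power × θ).

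The power values for AQoL-6D are assumptions, shown as a range. The last column holds the cost difference fixed and divides by the mean reported effect.

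| Power | θ | Calculation | Effect ratio | ICER relative to truth |
|---|---|---|---|---|
| 20% | 1.115 | 1 + (0.2791 − 0.0035)/(0.2 × 1.115) | 2.24 | 0.45 |
| 30% | 1.435 | 1 + (0.3475 − 0.0013)/(0.3 × 1.435) | 1.80 | 0.55 |
| 50% | 1.960 | 1 + (0.3989 − 0.0002)/(0.5 × 1.960) | 1.41 | 0.71 |
| 80% | 2.802 | 1 + 0.2800/(0.8 × 2.802) | 1.12 | 0.89 |

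Without the gate the ratio is 1.00 at every power.

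**3. If the tested quantity is not exactly the denominator.** The test is on AQoL-6D, while the denominator is QALYs. With equal standardised effects and correlation ρ between the two estimates, the ratio becomes 1 + ρ × (ratio − 1). At 20% power:
- ρ = 0.7: 1 + 0.7 × 1.24 = 1.87
- ρ = 0.5: 1 + 0.5 × 1.24 = 1.62

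**4. ARFS.** At 300 per arm (80% power) the ratio is 1.12. With the sexes pooled at 600 per arm, θ = 2.2 / (9.6 × √(2/600)) = 3.97, power is 97.8%, and the ratio is 1 + 0.053/(0.978 × 3.97) = 1.01.

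**5. The two triggers side by side.**

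| Result | Health Economic Analysis | Economic Measures, read literally |
|---|---|---|
| Both significant | Cost per QALY | ARFS or AQoL-6D, no order |
| Only AQoL-6D significant | Cost per QALY | All consequences beside costs |
| Only ARFS significant | Cost per ARFS point | All consequences beside costs |
| Neither significant | Cost-consequence | All consequences beside costs |

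The middle rows are not rare. With ARFS at 80% power, AQoL-6D at power q and independent results, exactly one is significant with probability 0.8(1 − q) + 0.2q. That is 77% at q = 5% (no AQoL-6D effect), 50% at q = 50% and 32% at q = 80%.

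**The case against.** The best defence is that the rule is prespecified and ordered, so the analyst has no free choice of outcome. That stands: this is not post hoc selection. It does not answer the point, because the bias comes from conditioning the ratio on significance, whoever fixed the condition and when.

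Four stronger readings are tempting, and the protocol does not support them.

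- *The two sections prescribe incompatible analyses.* Economic Measures asks for all consequences to be shown next to costs; it does not say an ICER is withheld. An ARFS ratio plus a full table would satisfy both sections, and *either* may be loose wording for *neither*. The wording mismatch and the missing order of measures remain.
- *The QALY information is lost or exaggerated.* AQoL-6D is a listed secondary outcome, and the cost-consequence branch sets incremental costs against all outcomes. What may be missing is the ratio.
- *At 20% power there is an 80% chance that cost per QALY is never reported.* This assumes both the power and a single governing test. If 20% power held for each intervention against control and any of the three comparisons opened the branch, simulation gives about 33% opening (28% if Group 2 has half of Group 3's effect), so about 67% to 72% unreported.
- *The ICER is badly biased whichever measure is used.* For ARFS the inflation is small.

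It is also fair to say that an article may leave particular displays of uncertainty to the full plan. Their absence is not criticised here.

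**Conclusion.** The concern holds in this form: the significance gate makes a reported ICER too favourable on average, and it drops the cost-per-QALY ratio on the strength of a test for which the trial was not sized.

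The size for AQoL-6D is uncertain because the protocol gives no effect, SD or power for it. The effect ratios of about 2.2 to 1.1 over 20% to 80% power assume one two-sided 5% test on the same quantity as the denominator; imperfect correlation makes them smaller. For ARFS the problem is minor at the planned power and negligible with the sexes pooled.

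The difference between the two triggers is a wording inconsistency to be reconciled, and the weaker part of the point. All of this bears on a secondary aim, and the primary ARFS efficacy analysis is untouched. The change should be made, but the trial's main conclusion does not depend on it.

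**What to change.** - Delete the significance conditions from both Economic Measures and Health Economic Analysis, and use one text in both places.
- Name the economic outcomes in advance: cost per QALY first, as Health Economic Analysis already orders them, with cost per ARFS point as a further analysis. It is the advance naming that cures the selection; this order simply keeps the plan's own priority.
- Report both ratios for all three pairwise comparisons whatever the p values, with the joint uncertainty in costs and effects. Bootstrapped cost-effect pairs would be one way to do this.
- Give the cost-consequence table alongside in every case.

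The cost is a wording change and modest programming. The AQoL-6D, ARFS and cost data are already planned, so no new data are needed. The downside is that some ratios will have wide uncertainty, particularly where the effect difference is near zero, and the report will have to show that.

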### Outcome Measures

Outcome measures will be completed via the Aim4Me website at baseline and at 3, 6, and 12 months, along with a process evaluation (Multimedia Appendix 2). In addition to text message and email reminders, participants may also receive a follow-up phone call to prompt the completion of questionnaires at follow-up time points.

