### Statistical Analysis

The outcome effects will first be evaluated using independent *t* tests, followed by repeated measures within-group changes in the ARFS diet quality score and modeling between-group changes over time using the generalized linear mixed model. The model will be fitted with ARFS at all follow-up points as the outcome variable, with fixed effects for group, time, baseline ARFS, and time by group interaction. Covariates, including PA, sleep, smoking, and social desirability, will be included in the statistical model as potential confounders. Statistical significance of the primary efficacy analysis will be based on Hochberg multiple testing procedures with a family-wise error rate for each time point held at 2.5%. The main analysis will use a generalized linear mixed model with the outcome at all time points and intention-to-treat principle. Sensitivity analyses will be conducted with the last observation carried forward, with multiple imputations, and for completers only. Analyses will be performed using SAS version 9.4 or later (SAS Institute Inc). All variables will be checked for plausibility and missing values. Data will be presented as mean (SD) for continuous and count variables.

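### The ICER denominator is set as an arithmetic mean difference with no stated baseline-utility adjustment, and the text leaves open whether the effect is a QALY total or a change score

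*Protocol article*

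**What the plan says.** The Health Economic Analysis section makes the economic method conditional. If AQoL-6D differs significantly, "a within-trial cost analysis will be conducted using quality-adjusted life years (QALYs) as the primary outcome", and "The incremental cost-effectiveness ratio (ICER) will report an incremental cost per QALY". The ratio is then given as a formula: the arithmetic mean cost difference "divided by the arithmetic mean difference in effect". Groups 2 and 3 are each compared with Group 1 and with each other. The next step is "If a significant change in AQoL-6D is not observed, the ARFS outcome measure will be used", and if neither measure is significant the method becomes a cost-consequence analysis.

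The Economic Measures section describes the outcome differently: "The economic analysis will use either the change in ARFS or AQoL-6D as the outcome of interest".

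Three other statements bear on this:

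- Outcome Measures: "Outcome measures will be completed via the Aim4Me website at baseline and at 3, 6, and 12 months". AQoL-6D is one of the secondary outcomes, and its description says that it yields utility scores.
- Statistical Analysis: the ARFS model is fitted "with fixed effects for group, time, baseline ARFS, and time by group interaction". No comparable statement is made for the economic outcome.
- Randomization: the strata are location, sex and BMI category. Utility is not among them.

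**The concern.** A 12-month QALY total depends on baseline utility in two ways: directly, as the start of the curve, and through the correlation of later utilities with the first. If one arm starts higher by chance, a plain difference in mean QALYs credits part of that head start to the intervention. Stratification does not restrain such an imbalance in utility, and the one adjustment described, for baseline ARFS, belongs to another outcome.

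Cost-effectiveness is part of the stated secondary aim. The arms differ by web feedback and one 30-minute consultation, so the QALY difference may well be small, and a ratio is sensitive to error in a small denominator. The change wording in Economic Measures does not settle the matter, since a change in utility is not a QALY, and subtracting baseline has its own residual imbalance.

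**Working it through.** **The plan's own figures.** The article states no figure for QALYs, AQoL-6D or the ICER. Only the sample size is needed here, and it reproduces. For a difference of 2.2 with SD 9.6, two-sided alpha 0.05 (two-sided assumed) and 80% power, n = 2 × (1.960 + 0.842)² × (9.6/2.2)² = 298.9, so 299 per arm (stated 300). Six cells of 300 give 1800, and 1800/0.70 = 2571 (stated 2570). Hence 2570/3 ≈ 857 per arm are randomised, and 857 × 0.70 ≈ 600 remain after the planned 30% loss at 12 months.

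**Assumptions not in the article.** AQoL-6D SD 0.15 to 0.25, equal at all visits; one common correlation r of 0.5 to 0.8 between any two visits; QALYs by the trapezoidal rule; AQoL-6D taken at all four time points (the detailed schedule is in an appendix that is not shown).

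**QALY weights.** For times 0, 0.25, 0.5 and 1 year the weights are 0.125, 0.25, 0.375 and 0.25, with sum 1 and sum of squares 0.28125.

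**Share of a baseline difference that reaches the effect estimate**

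- Unadjusted QALY difference: 0.125 + 0.875r. At r = 0.5 this is 0.5625; at r = 0.8 it is 0.825.
- QALY total less baseline utility: the same minus 1, that is -0.4375 and -0.175.
- Simple 12-month change in utility: r - 1, that is -0.50 and -0.20.
- Regression on baseline utility: 0 in expectation.

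**Size in QALYs.** The SE of the baseline difference is SD × √(2/n). The smallest value is 0.15 × √(2/857) = 0.0072 and the largest is 0.25 × √(2/600) = 0.0144. For a 1.96-SE imbalance:

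- Unadjusted, low end: 1.96 × 0.5625 × 0.0072 = 0.008.
- Unadjusted, high end: 1.96 × 0.825 × 0.0144 = 0.023.
- QALY total less baseline: about -0.002 (r = 0.8, SD 0.15, n = 857) to -0.012 (r = 0.5, SD 0.25, n = 600).

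**Precision.** In units of SD², the variance of one person's QALY is V = 0.28125 + 0.71875r. After regression on baseline it is V - (0.125 + 0.875r)².

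| r | V | After adjustment | Ratio |
|---|---|---|---|
| 0.5 | 0.641 | 0.324 | 0.51 |
| 0.6 | 0.713 | 0.290 | 0.41 |
| 0.8 | 0.856 | 0.176 | 0.21 |

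**Effect of the significance gate.** The correlation between the baseline difference and the unadjusted QALY difference is (0.125 + 0.875r)/√V, which is 0.70 at r = 0.5 and 0.89 at r = 0.8. Suppose there is no true effect and the gate is an unadjusted two-sided 5% test on QALYs (the article names no test). The mean absolute z among significant results is 0.0584/0.025 = 2.34. Such a result then carries an expected baseline imbalance in its own direction of 2.34 × 0.70 = 1.6 to 2.34 × 0.89 = 2.1 SE.

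**ARFS branch.** If the effect is a 12-month change in ARFS (SD 9.6 from the Sample Size section, same assumed r), the SE of the baseline difference is 9.6 × √(2/857) = 0.46 to 9.6 × √(2/600) = 0.55. A 1.96-SE imbalance leaves 1.96 × 0.20 × 0.46 = 0.18 to 1.96 × 0.50 × 0.55 = 0.54 points in the opposite direction, against a target difference of 2.2.

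**The case against.** The strongest reply is that the article never says raw or unadjusted. An arithmetic mean difference names the scale of the contrast and could be estimated by regression. QALY derivation and covariates may stand in a full economic plan that is not shown, and the section defers to best-practice guidelines. That stands as a limit: the plan cannot be said to exclude adjustment. It does, however, print a formula for the ratio, and read plainly that formula is a difference of arm means. The same article states baseline adjustment for ARFS and none here.

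A second reply is that the change wording already corrects for baseline. For ARFS it may remove much of an imbalance. For utility it makes the estimand less clear, since cost per QALY is promised, and subtraction overcorrects whenever r is below 1.

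Third, randomisation keeps the unadjusted difference unbiased. That is correct. What remains is precision, and bias conditional on the imbalance observed. An unadjusted gate adds to this, because it favours trials in which imbalance helped.

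Two stronger readings are tempting and not supported. A reader might infer that any baseline imbalance is counted in full as intervention effect; under the assumptions above only part of it is. A reader might also infer that carried-over imbalance would readily reverse the sign of the ICER. Cost per QALY is computed only after a significant AQoL-6D difference. If the gate uses the same unadjusted quantity, the denominator is at least 1.96 of its SEs, and removing a 1.96-SE baseline imbalance from a just-significant result shrinks it by 70% to 89% without reversing it.

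**Conclusion.** The point holds as a weakness in how the effect is specified, not as an invalid estimator. The article fixes the denominator as an arithmetic mean difference, states no baseline-utility term, and leaves unclear whether the effect is a QALY total or a change. Neither plain reading gives the baseline-adjusted estimate that the collected data allow. Adjustment would also cut the variance of the QALY difference by about 49% to 79%.

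All of these sizes rest on assumed AQoL-6D SDs, a common between-visit correlation and trapezoidal QALYs, and would change with other values. At 12 months about 600 per arm are expected, which makes the SEs about 20% larger than at full enrolment (√(857/600) = 1.20). The consequence is confined to the economic analysis, and for QALYs to the branch in which AQoL-6D is significant. It is worth correcting because the remedy is nearly free and the article reports data collection as ongoing.

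**What to change.** In the Health Economic Analysis section:

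1. Define QALYs as the area under the AQoL-6D utility curve over 0, 3, 6 and 12 months.
2. Estimate each between-group mean QALY difference by regression on group with baseline AQoL-6D as covariate, and use it as the ICER denominator. The numerator stays the arithmetic mean cost difference.
3. Use the same adjusted estimate for the significance gate that selects the QALY branch.
4. In the ARFS branch, use the baseline-adjusted ARFS difference.

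Then align the Economic Measures section, so that it names the QALY difference and the adjusted ARFS difference in place of a change.

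The cost is one added covariate and a few sentences. There is no new data collection and no change to the sample size.

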## Results

Data collection commenced in February 2018 and is ongoing. As of December 2019, 1277 participants have been randomized.

## Discussion

### Principal Findings

The aim of this study is to evaluate the efficacy of delivering varying levels of personalized dietary feedback and support on improving the diet quality of young adults. Young adulthood is a period of major transition whereby changes during this period influence diet and eating behaviors that contribute to the weight gain trajectory that is common in this age group. Changes include social influences, changes to the home and school/work environment, and changes in financial circumstances, which add additional stresses during this period. The perceived effort, cost, peer influence, lack of time, and feelings of inferiority are barriers to making positive changes in eating patterns and other health-related behaviors [17]. Further complexity is added when we start to consider the many other layers that shape a person’s eating behaviors, including the food and beverage industry, access to health care, education, and social and cultural norms, and it needs to be acknowledged that active engagement from various segments of society is required. Approaches need to be incorporated into existing organizational structures to influence change at the population level.

### Strengths and Limitations

This protocol has been designed to address some of the major challenges related to improving dietary patterns of young adults, including the ease of access to personalized nutrition advice, education on cooking skills, and practical nutrition strategies such as how to eat on a budget and goal setting and tracking to ensure dietary changes remain realistic and achievable. What is novel is the use of validated web-based dietary assessment tools to connect young adults with personalized real-time feedback on their dietary intake, an online library of resources about healthy eating, goal setting, and access to a health professional.

